### Study aims

Aim 1: Evaluate a novel portfolio of stable isotope-based tools for evaluating carbohydrate and protein digestion and amino acid absorption.

Aim 2: Test a novel non-invasive fluorescence sensor-based tool for real-time evaluation of gut permeability.

Aim 3: Characterise the microbiome and metabolome across well characterised and novel physiological sites (duodenal aspirate, duodenal mucus, duodenal tissue, stool, plasma, urine).

Aim 4: Quantify systemic and intestinal inflammation using established biomarkers of EE, immune cell phenotyping, epithelial PRR expression, and in vitro epithelial barrier models.

Aim 5: Determine if antibiotics, given intravenously, permeate into the gut lumen in sufficient quantities to modulate the microbiota.

All of these will be correlated with histological mucosal morphometry, lactulose permeation, and established biomarkers of EE.

### Study strengths and limitations

•A study of 80 adults with EE and 20 controls will develop novel analytical tools to demonstrate their viability and effectiveness for the assessment of gut functional capacity compared with current ‘gold standards’.•This study will inform future work on EE disease assessment and in treating children with severe acute malnutrition (SAM) and/or stunting.•These novel tools will have practical applications in clinical assessments not only in EE but other conditions that affect gut functional capacity allowing better understanding of the underlying mechanisms of different diseases.•A limitation of this study is the lack of country-specific controls in whom the same assays would be performed for comparison.•Including adults only in this study limits the applicability of some of the analytical methods when designing a child-based study due to smaller sample volumes.•The data will be generated over the course of a single 3-day protocol; analysis of longitudinal changes will require additional studies.

## Methods

### Study outcomes

The expected outcomes for each aim are shown in
Table 1.

**Table 1. T1:** Summary of outcomes with reference to study aims.

	Measured outcome	Detail
*Aim 1*	*Protein digestion and absorption using stable isotope tracers*	Assessment of ^13^C spirulina digestion (global index by breath ^13^CO _2_) and absorption using ^13^C Phe (from spirulina) and ^2^H labelled free Phe administered orally.
	*Bidirectional transmucosal amino acid flux (BTAAF)*	A novel tool involving dual infusion of differentially labelled amino acid tracers (Phe/Leu) orally and intravenously for the assessment of EE severity.
*Aim 2*	*Fluorescein*	A novel non-invasive measure of intestinal permeability using orally dosed fluorescein and a finger probe (transcutaneous fluorescence spectroscopy) for detection of systemically circulating fluorescein.
*Aim 3*	*Microbiome analysis*	I. Faecal species abundance and diversity indexes by 16s rRNA sequencing. II. In country deep metagenomic sequencing by long read (Nanopore) sequencing compared with other short-read platforms (Illumina). III. Evaluation of microbial communities in EE and their ability to uptake intestinal amino acids, including conversion of L-amino acids to D-forms.
	*Metabolic phenotyping*	I. Untargeted metabolomics ( ^1^H-NMR) of plasma, urine and faecal water. II. Targeted quantification (MS) of intestinal, plasma and urine amino acids (unlabelled + labelled) before and after administration of oral and intravenous stable isotopes.
	*Metaproteomic analysis*	1) Proteomic analysis of intestinal biopsies for expression of key mucosal proteins in biopsies (mucins and tight junction proteins including Zonulin, claudins and occludins). * 2) Dynamic proteomic analysis of key target proteins to assess mucosal and tight junction protein synthesis rates in biopsies by high-resolution MS and D2O labelling.
*Aim 4*	*Biomarker analysis*	Quantification of known markers of systemic inflammation, microbial translocation, and intestinal epithelial damage in plasma and stool.
	*Duodenal expression of PRR*	Profile the expression of bacterial, fungal, and viral PRR in the duodenal epithelium using immunohistochemistry.
	*Systemic immune cell analysis*	Characterisation of innate and adaptive systemic immune cell phenotypes using differential cell counting and flow cytometry.
	*Plasma and faecal cell cultures*	Evaluation of the immunogenic effect of PAMPs present in plasma and stool on epithelial barrier integrity and function using cell culture models.
*Aim 5*	*Antibiotic reverse permeation*	A novel technique for the assessment of reverse permeation of intravenously administered benzylpenicillin into the gut.
*Aim 6*	Compare all of the above with histological assessments of mucosal biopsies collected at endoscopy, lactulose/rhamnose testing, and established biomarkers of EE.	

* Does not give information on protein localisation.

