**Figure 1. f1:**
[figure not shown]
Domains of intestinal dysfunction leading to cycle of inflammation and persistence. Illustration of prominent elements of inflammation cycle, that includes (i) changes to gut microbiota diversity and pathobiome colonisation leading to decompartmentalization, which promotes (ii) epithelial barrier failure leading to increased permeability and (iii) microbial translocation of cell wall antigens and bacteria, which stimulates (iv) mucosal inflammation leading to (v) systemic inflammation which leads to increased demands for essential nutrients (e.g. amino acids), whose bioavailability may be limited by (vi) maldigestion caused by alterations to brush border architecture and enzyme activity and (vii) malabsorption caused by changes to the expression of nutrient transport proteins in epithelial cells. At the present time, it is not possible to determine how this network of functions is interrelated, and which functions are critical to resolve without new tools to assess each of these domains.

The urgent problem which we aim to address in the GI Tools study is the dearth of measurement tools to assess the gut functional capacity of communities affected by EE. These tools will 1) be essential for evaluating gut functional capacity in adults (across many disease states) 2) have the potential to assess gut functional capacity in children because of their largely non-invasive nature, and 3) direct the development of new therapeutic interventions to support optimal gut function, for example, recovery of children hospitalised with SAM.

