### Sample size estimation

As there are no, or very limited, data on these measurements in this population, the study was powered based on previous studies using stable isotope breath tests and permeability studies. Previous data from an enteropathy vs. healthy child cohort and
^13^C-sucrose breath tests
^
33
^ has suggested that calculating the cumulative
^13^CO
_2_ excretion, % relative to the dose, at 90 minutes post-intake best represents the villus integrity and the absorption capacity of only the small intestine. Preliminary data have shown that in a group of adults from Misisi with demonstrable sucrase-isomaltase (SI) expression in biopsies,
^
34
^ the mean cumulative % of dose excreted as
^13^CO
_2_ at 90 minutes is 20.29% compared to 16.02% in the group without SI expression, with SD of 5.29% – resulting in an effect size (ES) of 0.81.
^
34
^ With α = 0.05, power = (1-β) = 0.80 we estimate we need 20 samples per group for achieving 80% power with a one-tailed test. We will recruit 30 participants into the definitive studies, allowing for potential dropouts and incomplete sample sets. To estimate sample size for permeability studies we used data on circulating LPS concentrations in stunted children which were mean 481 EU/ml (SD 408) in Lusaka, compared to controls (mean 192, SD 113). This results in an effect size of 0.96, with α = 0.05 and power = 0.80 and we would require 18 in each group for a two-tailed test. The overall sample size was set at 80 adults to allow for sufficient power to cover a range of studies in adults and children.

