Table 3). Breath samples will be collected every 20 mins for the first 1 h and every 30 mins for the remaining 3 h. Blood samples will be collected into lithium heparin collection tubes via the intravenous cannula: 2 mL every 20 mins for the first 1 h and every 30 mins for the remaining 3 h, and 5mL for the last sample. Urine will be collected up to 180 mins (3 h) while saliva collected every 60 mins for 3 h. After 240 mins (4 h) the participant will be transferred to the endoscopy room where upper gastrointestinal endoscopy will be performed using doses of sedation with midazolam and pethidine selected by the endoscopist. Oximetry will be used throughout the procedure. During endoscopy, up to 10 mL of duodenal aspirate will be collected with clean tubing. Using the same tubing, 20 mL 0.9% of sterile saline will be used to collect duodenal lavage. A brushing will be collected using an endoscopic cytology brush, and then the brush will be cut off into 1000 μL PBS. For histology, 3 biopsies will be collected into normal saline using 2.8 mm biopsy forceps, orientated on cellulose acetate paper (Sartorius, Gottingen, Germany) in the endoscopy room and placed in formalin thereafter. An additional 5 biopsies will be collected into 3 cryovials (2+2+1). All samples collected during endoscopy, except for the 3 histology biopsies, will be snap-frozen in liquid nitrogen immediately after collection. At the end of day 3, the participant will be given urine and stool collection devices for the next day.

### Day 4

Only stool and urine samples will be collected.

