## Laboratory assessments

### Stable isotopes analysis

The
**
*non-radioactive
*
** stable isotope labelled amino acids are used to trace the digestion and absorption of protein (day 2) and bidirectional transmucosal amino acid flux (day 3). The labelling strategy is chosen to minimise isotopic crosstalk in the analysis and maximise the metabolic pools that can be sampled ethically. These include breath (
^13^CO
_2_), plasma (
^13^C /
^2^H amino acids), intestinal aspirates (
^13^C /
^2^H amino acids), and urine (
^13^C /
^2^H amino acids). Breath samples will be analysed using a Thermo Scientific™ Delta Ray™ Isotope Ratio Infrared Spectrometer (Thermo Fisher Scientific, Bremen, Germany) in the TROPGAN laboratory (breath
^13^CO
_2_) and
^13^C &
^2^H labelled amino acids analysed by a Agilent 1290 Infinity LC coupled to a 6560 triple quadrupole mass spectrometer (Agilent Technologies Inc., Cheadle, UK) in SUERC (
^13^C/
^2^H amino acid isotopologues).

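### Table 1 ties breath 13CO2 after 13C-spirulina to digestion, but the signal also carries absorption, amino-acid oxidation and CO2 output, so it cannot support a digestion-specific conclusion on its own

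*Protocol article*

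**What the plan says.** The Aim 1 row of Table 1 (Study outcomes) is headed as protein digestion and absorption. Within it, breath has one role, "Assessment of ^13^C spirulina digestion (global index by breath ^13^CO _2", and the phenylalanine tracers have another, "absorption using ^13^C Phe (from spirulina) and ^2^H labelled free Phe administered orally". The Stable isotopes analysis section says the labelled amino acids "trace the digestion and absorption of protein (day 2) and bidirectional transmucosal amino acid flux (day 3".

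Three other places bear on how the breath signal should be read:

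- The Figure 1 legend treats maldigestion and malabsorption as separate domains and describes "systemic inflammation which leads to increased demands for essential nutrients (e.g. amino acids".
- Sample size estimation, on 13C-sucrose, says that cumulative 13CO2 excretion "at 90 minutes post-intake best represents the villus integrity and the absorption capacity of only the small intestine".
- The Day 3 section says "Breath samples will be collected every 20 mins for the first 1 h and every 30 mins for the remaining 3 h". The Day 2 text gives the same intervals, while the Figure 2 legend gives 20 minutes for both days.

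The article describes no measurement of CO2 output and no rule for separating digestion from the later steps.

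**The concern.** Exhaled 13CO2 from a labelled protein is the end product of a chain: digestion, absorption, oxidation of the absorbed amino acids, and CO2 output. Table 1 attaches the result to the first link. The article's own reading of the sucrose breath test is in terms of villus integrity and absorption, so a breath result is not treated there as digestion alone.

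This matters because each tool is to be judged against morphometry, lactulose permeation and EE biomarkers. If the oxidised or exhaled fraction differs with EE severity, the breath index will correlate with severity even when digestion does not. If more amino acid goes to protein synthesis, 13CO2 falls and looks like maldigestion. If oxidation rises, 13CO2 rises and a real digestion defect is hidden. Even with no link to severity, between-person variation in the later steps dilutes a true digestion signal.

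**Working it through.** **1. Which samples could separate the steps**

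| Source | 13C in breath? | Needs digestion? |
|---|---|---|
| Day 2 13C-spirulina, oral | yes | yes |
| Day 2 free 2H8-Phe, oral | no | no |
| Day 3 free 13C6-Phe and 13C6-Leu, oral | yes | no |
| Day 3 intravenous Phe and Leu (deuterated) | no | not applicable |
| Day 3 arginine (15N label) | no | no |

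The Day 2 deuterated Phe cannot correct a 13C breath signal. It can serve as the free partner of spirulina-bound 13C-Phe in a body fluid. Day 2 blood is drawn before the drink and no post-dose blood is described that day. Urine is collected at 180 minutes, and Table 4 lists targeted isotope analysis of Day 2 urine. Day 3 breath reflects absorption, oxidation and CO2 output without a digestion step.

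**2. The plan's own breath figure**

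Sample size estimation gives 20.29% against 16.02% with SD 5.29%. The effect size is 4.27 / 5.29 = 0.807. One-sided at 5% with 80% power, a two-sample t-test needs 19.7, so 20 per group. The stated number reproduces and is not in dispute.

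**3. Illustration on that scale**

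Assumptions: the sucrose mean and SD apply to spirulina, digestion is identical in both groups, and only the fraction of absorbed label reaching breath is lower by r. Then d = 20.29 × r / 5.29.

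| r | d | Significant, one-sided, 20 per group | Significant, two-sided, 80 v 20 |
|---|---|---|---|
| 10% | 0.38 | 33% | 33% |
| 15% | 0.58 | 56% | 63% |
| 21% | 0.81 | 80% | 89% |
| 25% | 0.96 | 91% | 97% |

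The design difference is itself a relative drop of 4.27 / 20.29 = 21%.

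**4. Illustration as a correlation with severity**

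Assumptions (not in the documents): log-SD 0.25 for digestion (sD) and 0.25 for the later steps (sO).

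- Raw index with true digestion: sD / √(sD² + sO²) = 0.25 / 0.354 = 0.71.
- If digestion is unrelated to severity and the later steps correlate c with it, the spurious correlation is c × 0.71: 0.21 for c = 0.3 and 0.35 for c = 0.5. With n = 80 and the Fisher z test, it is significant in 47% and 90% of studies at two-sided 5%, and in 18% and 67% at 0.5%.

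**5. Does Day 3 breath help?**

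Let m be the log-SD of the mismatch between the Day 3 signal and the Day 2 later steps.

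- Fixed Day 2:Day 3 ratio: r = sD / √(sD² + m²).
- Covariate adjustment, with slope sO² / (sO² + m²): r = sD / √(sD² + sO²m² / (sO² + m²)).

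| m | Raw | Ratio | Adjusted |
|---|---|---|---|
| 0.10 | 0.71 | 0.93 | 0.94 |
| 0.15 | 0.71 | 0.86 | 0.89 |
| 0.25 | 0.71 | 0.71 | 0.82 |
| 0.30 | 0.71 | 0.64 | 0.79 |

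The ratio breaks even when m equals sO and is worse beyond it. The adjusted index is at least as good as the raw one throughout. It is still partial: at m = 0.30 the slope is 0.0625 / 0.1525 = 0.41, and the spurious correlation falls only from 0.21–0.35 to 0.14–0.23.

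**6. Denominators**

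Table 3 gives the Day 3 oral amino acids in µmol per kg and the Day 3 text in mmol per kg, a 1000-fold difference. For Day 2 free 2H8-Phe the text gives 0.035 mg per kg, which is 2.1 mg at an assumed 60 kg, and Table 3 gives 200 mg, about 95-fold more. The Day 2 and Day 3 text places breath sampling after dosing and mentions no pre-dose breath sample.

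**The case against.** A reader might infer that Aim 1 has no means of telling maldigestion from altered oxidation. The documents do not support that. The same drink carries bound 13C-Phe and free 2H-Phe; only the bound form needs digestion, and later handling is largely shared. Their ratio addresses digestion, although Table 1 assigns the pair to absorption and post-dose urine is the fluid left to carry it on Day 2.

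A reader might also infer that the protocol itself predicts oxidation will move with severity. The Figure 1 legend speaks of demand for amino acids; it says nothing of oxidation or the direction of 13CO2, and it says the relations between these functions cannot yet be determined.

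Third, the row heading and the term global index soften the label, Table 1 is a summary without a formula, and the Discussion warns that isotope data need careful physiological interpretation. This is fair, and a breath formula may properly sit in an analysis plan. But none of these passages names oxidation or CO2 output, and the row still ties breath to digestion.

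Fourth, the planned multiplicity correction would lower the false-positive rates, as the 0.5% column of results shows, but not remove the bias.

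Finally, Day 3 is an imperfect reference: a bolus plus sips of two amino acids against a single protein drink. That objection stands against a fixed ratio. It limits covariate adjustment without defeating it.

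**Conclusion.** The point holds as a matter of what the breath index measures. As worded, Table 1 invites a digestion conclusion from a signal that mixes digestion with absorption, oxidation and CO2 output, and such a conclusion could be wrong in either direction. The bias cannot be sized from the documents. The figures above show only that modest differences would be enough: a 10–25% shift in the exhaled fraction gives d of 0.38–0.96 on the borrowed sucrose scale, and assumed correlations of 0.3–0.5 give a spurious r of 0.21–0.35. All variances, correlations and mismatches are assumptions. It does not follow that Aim 1 fails or that a plain Day 2:Day 3 ratio should be the digestion outcome; with a between-day mismatch of 0.25 or more that ratio gains nothing or loses.

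**What to change.** 1. In Table 1, relabel raw Day 2 13CO2 recovery as a combined protein digestion-absorption-oxidation index, and rest no digestion-specific conclusion on it alone.
2. Base digestion statements on the bound 13C-Phe to free 2H-Phe ratio in the Day 2 post-dose urine.
3. As support, analyse Day 2 log 13CO2 recovery with the same participant's Day 3 log 13CO2 recovery as a regression covariate, not as a fixed divisor, and show raw and adjusted results side by side.
4. Before either breath index is expressed as percent of dose, reconcile the passages on tracer amounts (Day 3 µmol against mmol per kg; Day 2 2H8-Phe per-kg against fixed amount) and confirm a pre-dose breath sample on both days.

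The cost is mainly wording and one extra model, since the urine and both days' breath samples are already planned; a pre-dose breath sample would be a small addition if it is not already taken. The downsides should be stated: Day 3 noise leaves the correction partial, Phe and Leu oxidation only approximates that of all spirulina amino acids, the two days differ in dosing pattern, and the urine ratio rests on a single post-dose collection.

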## Materials and analysis

### Study design

This cross-sectional study will be conducted in adults in Zambia using a range of stable isotope labelled amino acids and fluorescent tracers,
^
1
^
^,^
^
30
^ systemic immune assessments, EE biomarker analysis, microbiome and metabolome analysis, enzyme functional capacity, proteomics and metaproteomic analysis, barrier integrity and function capacity analysis using cell lines, antibiotic reverse permeation, duodenal morphometry, and duodenal expression of PRR to identify potential new tools for measuring gut functional capacity in Zambian adults with EE.

In a sub-study in Zimbabwean adults, we will explore the extent to which antibiotics leak from systemic circulation into the gut, where they may modulate the microbiota.
^
31
^ The study will be carried out in Harare, where sampling of caecal luminal fluid collected at colonoscopy will be used to quantify reverse permeation of intravenously administered benzylpenicillin from the systemic circulation into the gut lumen. Future work will focus on refinement and simplification of these techniques to make them suitable for use in children.

### Study population

The initial study will be conducted in 80 adults from a population in Lusaka, Zambia, where our previous studies have demonstrated that EE is virtually ubiquitous in adults and children.
^
32
^ Additionally, 20 controls living in high socioeconomic status (SES) residential areas (Rhodes Park, Longacres, Kabulonga, Ibex Hill, Chelston, Avondale, Sunningdale, Roma, Chamba Valley, Lilayi, New Kasama and others) within Lusaka will be included. A further 20 patients attending for routine colonoscopy (for diagnostic purposes) in Harare, Zimbabwe will be enrolled for the antibiotic permeation study. As these participants will already be booked for colonoscopy they will be drawn from higher socio-economic groups.

### Sample size estimation

As there are no, or very limited, data on these measurements in this population, the study was powered based on previous studies using stable isotope breath tests and permeability studies. Previous data from an enteropathy vs. healthy child cohort and
^13^C-sucrose breath tests
^
33
^ has suggested that calculating the cumulative
^13^CO
_2_ excretion, % relative to the dose, at 90 minutes post-intake best represents the villus integrity and the absorption capacity of only the small intestine. Preliminary data have shown that in a group of adults from Misisi with demonstrable sucrase-isomaltase (SI) expression in biopsies,
^
34
^ the mean cumulative % of dose excreted as
^13^CO
_2_ at 90 minutes is 20.29% compared to 16.02% in the group without SI expression, with SD of 5.29% – resulting in an effect size (ES) of 0.81.
^
34
^ With α = 0.05, power = (1-β) = 0.80 we estimate we need 20 samples per group for achieving 80% power with a one-tailed test. We will recruit 30 participants into the definitive studies, allowing for potential dropouts and incomplete sample sets. To estimate sample size for permeability studies we used data on circulating LPS concentrations in stunted children which were mean 481 EU/ml (SD 408) in Lusaka, compared to controls (mean 192, SD 113). This results in an effect size of 0.96, with α = 0.05 and power = 0.80 and we would require 18 in each group for a two-tailed test. The overall sample size was set at 80 adults to allow for sufficient power to cover a range of studies in adults and children.

### Participant recruitment

For adults from Misisi compound, consent will begin with an invitation delivered door-to-door, while social media approaches, like Facebook and/or Instagram will be used for the controls. All household members eligible to participate will be invited to group discussions. The study group discussion meetings will include the following:
•Introduction to the study team.•Introduction to the study rationale and protocol in full; explanation of the study.•Reading of participant information sheet in Nyanja or Shona; literacy rates in Misisi and Harare are variable, and this is therefore the most appropriate method for conveying this information.•Benefits and risks of being involved in the research.•Previous participants’ descriptions of being involved in research which includes endoscopy.•Questions to previous participants.•Questions to the study team regarding the study.•Invitation to attend a guided tour of the research and endoscopy facilities.

Potential participants who are unable to make any of the focus group meetings will be invited to the field clinic to discuss the information sheet and study procedures with a member of the study team. All potential participants will be invited to provide written informed consent in individual interviews with a member of the study team afterwards. They will be invited to ask further questions or express concerns. If happy to proceed, they will be asked to sign or thumbprint the consent form, which will be read out to them in the language of their choice if they are unable to read. Consenting and enrolment will occur at least 48 hours after they have attended a focus group meeting or study explanation visit. Only participants who give consent will undergo screening and enrolment into the study. However, if for any reason during the study, the participant decides to withdraw, they will be allowed to exit the study but will not be replaced. In the event of withdrawal, participants will have a choice whether their samples can be retained or must be destroyed.

